## Abstract

**Background:**

Previous pharmacokinetic trials suggested that 40 mg subcutaneous enoxaparin once daily provided inadequate thromboprophylaxis for intensive care unit patients. Critically ill patients with acute kidney injury are at increased risk of venous thromboembolism and yet are often excluded from these trials. We hypothesized that for critically ill patients with acute kidney injury receiving continuous renal replacement therapy, a dose of 1 mg/kg enoxaparin subcutaneously once daily would improve thromboprophylaxis without increasing the risk of bleeding. In addition, we seek to utilize urine output prior to discontinuing dialysis, and low neutrophil gelatinase-associated lipocalin in dialysis-free intervals, as markers of renal recovery.

**Methods/Design:**

In a multicenter, double-blind randomized controlled trial in progress at three intensive care units across Denmark, we randomly assign eligible critically ill adults with acute kidney injury into a treatment (1 mg/kg enoxaparin subcutaneously once daily) or control arm (40 mg enoxaparin subcutaneously once daily) upon commencement of continuous renal replacement therapy.

We calculated that with 133 patients in each group, the study would have 80% power to show a 40% reduction in the relative risk of venous thromboembolism with 1 mg/kg enoxaparin, at a two-sided alpha level of 0.05. An interim analysis will be conducted after the first 67 patients have been included in each group.

Enrolment began in March 2013, and will continue for two years. The primary outcome is the occurrence of venous thromboembolism. Secondary outcomes include anti-factor Xa activity, bleeding, heparin-induced thrombocytopenia, filter lifespan, length of stay, ventilator free days, and mortality. We will also monitor neutrophil gelatinase-associated lipocalin and urine volume to determine whether they can be used as prognostic factors for renal recovery.

**Discussion:**

Critically ill unit patients with acute kidney injury present a particular challenge in the provision of thromboprophylaxis. This study hopes to add to the growing evidence that the existing recommendation of 40 mg enoxaparin is inadequate and that 1 mg/kg is both safe and effective for thromboprophylaxis.

In addition, the study seeks to identify predictors of renal recovery allowing for the proper utilization of resources.

**Trial Registration:**

EU Clinical Trials Register: EudraCT number: 2012-004368-23, 25 September 2012.

## Background

Approximately 30% of critically ill patients admitted to an intensive care unit (ICU) develop acute kidney injury (AKI) [1]. Biomarker neutrophil gelatinase-associated lipocalin (NGAL) is associated with the development of AKI, the need for dialysis, and mortality [1-4].

Despite ICU patients receiving recommended doses of prophylactic low- molecular-weight heparin (LMWH), between 5 and 15.5% develop proximal leg deep-vein thrombosis (DVT) [5,6]. ICU patients with AKI frequently have activated coagulation pathways triggered by increased tissue factor and fibrinogen, reduced fibrinolysis, activation of endothelial surfaces, and thrombocytes. Thus such patients have a four-fold higher risk for developing venous thromboembolism (VTE) compared with ICU patients without renal insufficiency [7-9]. Critically ill patients with AKI are also predisposed to bleeding because of uremic platelet dysfunction, coagulopathies, and comorbidities. However many bleeding episodes are deemed as minor [10,11].

Major or fatal bleeding is very rare in the ICU, whereas VTE is relatively more common. VTE may not be detected in the ICU patient population as the symptoms are often minimal or atypical [12-14]. In many studies high-dose enoxaparin yields high peak and trough anti-factor Xa (anti-X_a_) values, but no increase in bleeding complications regardless of the degree of renal insufficiency [15]. A delay in starting thromboprophylaxis was associated with an increased risk of mortality in patients on the ICU [16]. Thus, the risk-benefit ratio seems to favor use of anticoagulant thromboprophylaxis [10].

In a recent study, we showed that a weight-based dose of enoxaparin subcutaneous (sc) once daily (QD) contrary to the standard dose of 40 mg enoxaparin sc QD yielded satisfactory levels of anti-X_a_ for critically ill patients, was more likely to maintain anti-X_a_ levels within the therapeutic range for longer periods of time and did not result in bioaccumulation [17].

The primary objective of this study is to reduce the incidence of VTE among AKI patients on continuous renal replacement therapy (CRRT) by using 1 mg/kg enoxaparin sc QD, versus the standard dose of 40 mg enoxaparin sc QD. We hypothesized that higher doses of enoxaparin would optimize thromboprophylaxis without increasing the risk of bleeding in these patients. Secondary objectives of the trial include examining the utility of neutrophil gelatinase-associated lipocalin (NGAL) levels and urine output as predictors of renal recovery.

## Methods/Design

### Trial design

This is a multicenter randomized controlled trial conducted at three ICUs across Denmark to assess whether a dose of 1 mg/kg enoxaparin versus standard dose of 40 mg enoxaparin will improve thromboprophylaxis in AKI patients on CRRT, without increasing the risk of bleeding. We will randomly assign eligible critically ill adults with AKI into a treatment arm (1 mg/kg enoxaparin sc QD) or a control arm (40 mg enoxaparin sc QD) upon commencement of CRRT. The sample population will consist of 133 patients from ICUs at Odense University Hospital (OUH), Svendborg Hospital, and SVS Esbjerg Hospital. An interim analysis will be conducted after the first 67 patients have been included in each group. Enrolment began in March 2013 and will continue until March 2015. Patients will be followed until either: (1) a combination of VTE and renal recovery, (2) a combination of heparin - induced thrombocytopenia (HIT) and renal recovery, (3) ICU death or discharge, or (4) change from continuous to intermittent dialysis. Investigators will obtain consent for the collection of data on treatments and outcomes for participants who withdraw prematurely from the project. Many of the current investigators have participated in other trials and, as such, have a proven track record with respect to enrolment and follow-up of participants and collecting complete data sets. We will document the reasons for missing data, collect auxiliary variables that may predict outcome and/or determine which patients are more susceptible to dropout, and follow-up on all such patients until 24 hours after the last dose of enoxaparin.

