	Enoxaparin will be administered subcutaneously to the thigh or abdomen of the study patients from the day of inclusion, until the end of each participant’s study period.
Key inclusion and exclusion criteria	Inclusion criteria: patients are eligible if they give consent, develop acute kidney injury, need continuous renal replacement therapy, weigh 45 to 150 kg, and are ≥18 years.
	Exclusion criteria: these include a) admission diagnosis of major trauma, b) need for therapeutic anticoagulation, c) contraindication to heparin (allergy or heparin-induced thrombocytopenia), d) pregnancy, e) life-support limitation, f) uncontrolled hypertension (bp > 180/110) for at least 12 hours, g) cerebral hemorrhage/acute gastrointestinal bleed, h) severe thrombocytopenia (platelet count <50 × 109/l), i) International Normalized Ratio (INR) or activated partial thromboplastin time (APTT) ≥2 times the upper limit of normal, j) chronic renal failure or acute-on-chronic renal failure, and k) initial evaluation more than 24 hours after commencement of continuous renal replacement therapy.
Study type	Interventional allocation: randomized
	Intervention model: double arm
	Masking: double blind (subject, relatives, investigator, outcomes assessor)
	Primary purpose: prevention
Date of first enrolment	March 2013
Target sample size	266
Recruitment status	Recruiting
Primary outcome(s)	Venous thromboembolism
Key secondary outcomes	Catheter-related thrombus, anti-Xa activity, bleeding, heparin-induced thrombocytopenia, filter lifespan, length of stay, ventilator free days, and mortality. We will monitor neutrophil gelatinase-associated lipocalin levels and urine volume to determine whether they can be used as prognostic factors for renal recovery.

**Table 2 T2:** Protocol revision chronology

**Date**	**Protocol amendment**
Original version, 22.02.2011	Amendment Number 1:
	Primary reason for amendment:
	Changes in the methods sections - a decision to allow the pharmacy at OUH to generate randomization code was made.
Version 2, 18.05.2011	Amendment Number 2:
	Primary reason for amendment:
	At the request of GCP changes in the ethics section to elaborate on the procedure for obtaining consent.
Version 3, 18.07.2012	Amendment Number 3:
	Primary reason for amendment:
	The methods section was amended to include a description of the conduct of CRRT during the trial.
Version 4, 25.08.2012	Amendment Number 4:
	Primary reason for amendment:

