### Sample size and statistical methods

We hypothesized that the optimal dose of enoxaparin would reduce the incidence of VTE in critically ill AKI patients requiring CRRT without causing an increase in bleeding. An additional hypothesis was that high urine output prior to the discontinuation of dialysis and low NGAL in dialysis-free intervals can predict renal recovery in these patients.

We estimated that with 133 patients in each group the study would have 80% power to show a 40% reduction in the relative risk of VTE with 1 mg/kg enoxaparin sc QD, assuming an incidence rate of 40% in the control group, at a two-sided alpha level of 0.05. An interim analysis (for both safety and efficacy) after approximately 50% of the patients have completed the study will be performed by an independent statistician blinded to the treatment allocation. These outcomes will be analyzed with stopping rules based on the Fleming-Harrington-O’Brien stopping boundary using *P* = 0.01, with adjustment for an overall type 1 error of 0.05, and with the final analysis conducted at *P* = 0.045 [21]. The statistician will report, in strict confidence, to the DMC (see Table 3). The DMC members will not be blinded to patient allocation. They may request other analyses (such as data from other comparable trials) prior to reaching a decision on the continuation of the trial. The DMC will report its recommendations in writing to the Trial Steering Committee. The study can also be terminated if the difference between groups is negligible and the statistician using ’conditional power’ calculation determines that continuation will be futile.

**Table 3 T3:** Organizational structure and responsibilities

**Title**	**Name(s)**	**Function(s)**
Principal investigator and Research Physician	[name], MB, BS; EDIC	Design and conduct of trial F.B.I., protocol preparation and revisions, preparation of Case Report Forms, managing Clinical Trials Office, publication of study reports,member of both committees, and organization of steering committee meetings.
Lead investigators	[name], MB, BS; EDIC Odense University Hospital	Maintain trial master file and resolve contractual issues at sites
	[name], Phd	
	Svendborg Hospital	
	[name] [name] SVS Esbjerg Hospital	Responsible for identification, recruitment, data collection, and completion of CRFs, along with follow-up of study patients and adherence to study protocol.
Steering committee	[name], MB ,BS; EDIC	Agreement of final protocol

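### The Trial design section gives the sample as 133 patients, but the power calculation, the abstract and Table 1 require 133 per group (266); the interim trigger is also worded in two ways

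*Protocol article*

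**What the plan says.** **Sample size.** Four places in the protocol article give it:

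- Trial design: "The sample population will consist of 133 patients from ICUs at Odense University Hospital (OUH), Svendborg Hospital, and SVS Esbjerg Hospital". Nothing says that this is a per-group figure.
- Abstract, Methods/Design: "We calculated that with 133 patients in each group, the study would have 80% power".
- Sample size and statistical methods: "We estimated that with 133 patients in each group the study would have 80% power".
- Table 1, under Ethics: "Target sample size 266".

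**Interim timing.** Trial design, directly after the sentence on 133 patients, says: "An interim analysis will be conducted after the first 67 patients have been included in each group". The abstract uses the same trigger. The sample size section says instead: "An interim analysis (for both safety and efficacy) after approximately 50% of the patients have completed the study". That section sets the thresholds at P = 0.01 for the interim and P = 0.045 for the final analysis, for an overall type 1 error of 0.05. It also allows a stop for futility based on conditional power.

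**The concern.** Trial design is where a reader looks for the size of the trial, and as written it gives half the number on which the power rests. The recruitment target, the half-way point for the interim and the conditional-power calculation all depend on the final sample size. With a total of 133, the planned interim would fall after the last patient.

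The interim wording matters because inclusion and completion are different events. Follow-up runs until ICU death or discharge, a change to intermittent dialysis, or VTE or HIT combined with renal recovery. Under Outcome measures, a leg DVT counts towards the primary outcome only if it is detected 3 days or more after randomization. The most recently included patients therefore cannot yet have a complete primary outcome. An interim cut at the 134th inclusion would hold less information than one cut when half the patients have finished.

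**Working it through.** **Inputs**, all from Sample size and statistical methods: control VTE incidence 0.40; relative risk reduction 40%, so 0.40 × 0.60 = 0.24 in the 1 mg/kg arm; two-sided alpha 0.05; power 80%; interim threshold 0.01; final threshold 0.045. Allocation is taken as 1:1 from the equal group sizes.

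**1. Reproduce the stated figure.** Two proportions, pooled variance under the null, no continuity correction:

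n per group = [z(0.975)·√(2p̄(1−p̄)) + z(0.80)·√(p₁(1−p₁) + p₂(1−p₂))]² / (p₁−p₂)²

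- p̄ = (0.40 + 0.24)/2 = 0.32, so √(2 × 0.32 × 0.68) = √0.4352 = 0.6597
- √(0.24 + 0.1824) = √0.4224 = 0.6499
- n = [1.960 × 0.6597 + 0.8416 × 0.6499]² / 0.16² = 1.840² / 0.0256 ≈ 132.3, rounded up to **133 per group**

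The article's 133 is therefore a per-group number.

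**2. Power under each reading.** Power = Φ{[0.16·√n − 1.960 × 0.6597] / 0.6499}

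| Reading | n per group | Power at 0.05 |
|---|---|---|
| 133 in each group | 133 | Φ(0.850) = 80.2% |
| 133 in total | 66.5 | Φ(0.018) = 50.7% |

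At the final threshold of 0.045 taken as a single test, the figures are 78.9% and 48.9%. Counting both looks, power at 133 per group is 80.2% (unpooled variance, interim at half information). The interim plan does not undermine the stated power.

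**3. Internal check in Trial design.** 67 per group × 2 = 134, which exceeds 133. Against the per-group figure, 67/133 = 50.4%. The interim sentence makes sense only if 133 is per group.

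**4. Overall alpha of the two thresholds.** With information fraction t at the interim, the two test statistics are bivariate normal under the null with correlation √t, and overall alpha = 1 − P(|Z₁| < 2.576, |Z₂| < 2.005).

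| t | Overall two-sided alpha |
|---|---|
| 0.60 | 0.0487 |
| 134/266 = 0.504 | 0.0498 |
| 0.50 | 0.0498 |
| 0.45 (assumed) | 0.0504 |
| 0.40 (assumed) | 0.0509 |
| 0.30 (assumed) | 0.0519 |

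The pair holds 0.05 from about 48% information upward. The article does not say how many outcomes would be pending at the 134th inclusion, so the fractions below one half are assumptions.

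**5. How plausible the low fractions are.** The plan is 266 patients in 24 months, or 266/24 ≈ 11 per month. For t = 0.40 at the 134th inclusion, 134 − 0.40 × 266 ≈ 28 patients would still be in follow-up, which implies a mean follow-up of about 2.5 months. If mean follow-up is assumed to be 2 to 4 weeks, about 5 to 10 outcomes are pending, t is about 0.485 to 0.465, and overall alpha is 0.0500 to 0.0502.

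**The case against.** The strongest reply is that this is a dropped phrase. The abstract, the sample size section and Table 1 agree on 133 per group or 266, the calculation reproduces, and the interim sentence itself rules out a total of 133. On this view nobody would run the trial at 133, and the 51% power describes a design that nobody planned. That is fair as to consequence: the power calculation needs no change. The section that defines the design is still wrong as written.

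On timing, the two descriptions can be read together: 67 included per group as a recruitment milestone, and half completed as the condition for analysis. This is a reasonable reading, but the article does not state it, and the two events differ whenever patients are still being followed.

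A reader might go further and infer three things that the document does not support:

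- **That the included trigger breaks the stated alpha.** The thresholds give 0.0498 at half information and hold 0.05 from about 48% upward. Exceeding it needs an assumed lower fraction, and even at 30% the excess is only about 0.002.
- **That the final threshold of 0.045 must be recalculated.** Nothing in the article makes it wrong at the planned half-way point.
- **That counting 67 per group breaches the blind.** The pharmacy generated the sequence, the DMC is unblinded, and blocks of four keep the arms close to equal. A trigger counted in total is simpler, but no breach is shown.

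**Conclusion.** The sample size in Trial design is wrong as written. It conflicts with three other places in the article and with its own next sentence. The figure consistent with the stated 80% power is 133 per group, 266 in total (80.2%); 133 in total would give 50.7%. These figures rest on the article's own rates of 40% and 24%, two-sided alpha of 0.05, 1:1 allocation and a pooled two-proportion test.

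The interim trigger is a smaller inconsistency of wording that should be settled in the same edit. Its effect on type 1 error is very small: 0.0504 at an assumed 45% information and 0.0509 at an assumed 40%, against about 0.0498 at half. Neither the power calculation nor the 0.01/0.045 thresholds are shown to be in error.

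**What to change.** In Trial design, replace the total with 266 patients (133 in each group) from the three hospitals.

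Use one interim trigger, counted in total, in the abstract, Trial design and the sample size section: the interim analysis takes place when 134 randomized patients (about 50%) have completed primary-outcome follow-up.

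The 0.01 and 0.045 thresholds then stand. The change costs a few sentences, with no extra patients and no new calculation.

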### Ethics

Ethical approval for this protocol was obtained from the Danish national scientific ethical committee (reference number: 1210528) and the study was also approved by Danish Health and Medicines Authority (reference number: 2012100176) (see Tables 1 and 2). The study will comply with the ethical principles set forth in the Declaration of Helsinki and will be conducted in accordance with good clinical practice. Funding sources for this research had no role in the design of this study and will have no authority over data collection, analysis, interpretation, or reporting of this study.

**Table 1 T1:** World Health Organization trial registration data set

**Data category**	**Information**
Primary registry and trial identifying number	EU clinical trials register:
	EudraCT number: 2012-004368-23
Date of registration in primary registry	25/09/2012
Secondary identifying numbers	Danish health and medicines authority: 2012100176
	Danish national scientific ethical committee: 1210528 Sponsor's protocol number 20121005
Source(s) of monetary or material support	Danish society of anesthesiology & intensive medicine’s research initiative
	Odense University Hospital’s research grant
	Lippmann fund
Primary sponsor	[name], Professor at the department of Anesthesiology and Intensive Care at Odense University Hospital, Odense, Denmark.
Secondary sponsor(s)	N/A
Contact for public queries	[name], MB, BS; EDIC
	Odense University Hospital
	Department of Anesthesiology and Intensive Care
	[name]
	[name]
	[contact]
	Email: [contact]
Contact for scientific queries	[name], MB, BS; EDIC
	Principal investigator
	Odense University Hospital
	Department of Anesthesiology and Intensive Care
	[name]
	[name]
	[contact]
	Email: [contact]
Public title	A feasible strategy for preventing blood clots in critically ill patients with acute kidney injury (FBI)
Scientific title	A feasible strategy for preventing blood clots in critically ill patients with acute kidney injury (FBI) - prospective randomized, double-blind multicenter study
Countries of recruitment	Denmark
Health condition(s) or problem(s) studied	Venous thromboembolism, enoxaparin dose, acute kidney injury, bleeding
Intervention(s)	Treatment arm: 1 mg/kg enoxaparin subcutaneous once daily
	Control arm: 40 mg enoxaparin subcutaneous once daily
	Enoxaparin will be administered subcutaneously to the thigh or abdomen of the study patients from the day of inclusion, until the end of each participant’s study period.
Key inclusion and exclusion criteria	Inclusion criteria: patients are eligible if they give consent, develop acute kidney injury, need continuous renal replacement therapy, weigh 45 to 150 kg, and are ≥18 years.
	Exclusion criteria: these include a) admission diagnosis of major trauma, b) need for therapeutic anticoagulation, c) contraindication to heparin (allergy or heparin-induced thrombocytopenia), d) pregnancy, e) life-support limitation, f) uncontrolled hypertension (bp > 180/110) for at least 12 hours, g) cerebral hemorrhage/acute gastrointestinal bleed, h) severe thrombocytopenia (platelet count <50 × 109/l), i) International Normalized Ratio (INR) or activated partial thromboplastin time (APTT) ≥2 times the upper limit of normal, j) chronic renal failure or acute-on-chronic renal failure, and k) initial evaluation more than 24 hours after commencement of continuous renal replacement therapy.
Study type	Interventional allocation: randomized
	Intervention model: double arm
	Masking: double blind (subject, relatives, investigator, outcomes assessor)
	Primary purpose: prevention
Date of first enrolment	March 2013
Target sample size	266
Recruitment status	Recruiting
Primary outcome(s)	Venous thromboembolism
Key secondary outcomes	Catheter-related thrombus, anti-Xa activity, bleeding, heparin-induced thrombocytopenia, filter lifespan, length of stay, ventilator free days, and mortality. We will monitor neutrophil gelatinase-associated lipocalin levels and urine volume to determine whether they can be used as prognostic factors for renal recovery.

**Table 2 T2:** Protocol revision chronology

**Date**	**Protocol amendment**
Original version, 22.02.2011	Amendment Number 1:
	Primary reason for amendment:
	Changes in the methods sections - a decision to allow the pharmacy at OUH to generate randomization code was made.
Version 2, 18.05.2011	Amendment Number 2:
	Primary reason for amendment:
	At the request of GCP changes in the ethics section to elaborate on the procedure for obtaining consent.
Version 3, 18.07.2012	Amendment Number 3:
	Primary reason for amendment:
	The methods section was amended to include a description of the conduct of CRRT during the trial.
Version 4, 25.08.2012	Amendment Number 4:
	Primary reason for amendment:
	Fleming-Harrington-O’Brien stopping rule and futility measure via ’conditional power’ calculation was introduced.
Version 5, 31.08.2012	Amendment Number 5:
**Version 5 was the first version to be submitted to the Danish Health and Medicines Authority and the Danish national scientific ethical committee.**	Primary reason for amendment:
	The comparator dose which was unconfirmed until this point was included in this new protocol version.
	At the request of Danish Health and Medicines Authority changes were made to the exclusion criteria so that patients with chronic renal failure or acute-on-chronic renal failure were ineligible. The methods section was also updated to indicate that a patient who changed from CRRT to intermittent hemodialysis would have reached the end of the study period. In addition, further details about the reporting of adverse events were included.
Version 6, 21.01.2013	Amendment Number 6:
	Primary reason for amendment:
	At the request of the Danish national scientific ethical committee a separate information sheet for the designated surrogates was developed.
	The methods section was also revised due to the acquisition of new dialysis machines at OUH.
Version 7, 06.06.2013	Amendment Number 7:
	Primary reason for amendment:
	A change in the exclusion criteria:
	platelet count of <75× 109/l, changed to <50 × 109/l and INR or APTT ≥1½ times the upper limit of normal changed to ≥2 times the upper limit of normal.

Issue date: 06 June 2013. Protocol Amendment Number: 07. Authors: [name], MB BS; EDIC; [name]; [name] [name]; [name]; [name], DMSc. OUH, Odense University Hospital; GCP, Good Clinical Practice; CRRT, Continuous renal replacement therapy; APTT, Activated partial thromboplastin time; INR, International normalized ratio.

Research physicians on the ICUs of the aforementioned three hospitals will obtain written informed consent from all potential trial participants or their designated surrogates for participation in the study. The participants will then be randomized following recruitment and clinical interviews. For those who suffer harm from trial participation, there is the possibility to appeal and receive compensation according to the Act on the Right to Complain and Receive Compensation within the Danish health service. At the end of the trial, participants who indicate on the consent form that they wish to be informed of the results will be contacted by the trial sponsor. The model consent form and other related documents given to participants and designated surrogates are provided as supplements to this protocol (Additional file 1, Additional file 2, and Additional file 3).

All laboratory specimens, reports, data forms, and other study-related information are identified by a coded number only. These are stored separately from participant-related information, both in locked file cabinets in areas with limited access. The web-based FBI database (Department of Health Cooperation and Quality Database Unit, Region of Southern Denmark, Vejle, Denmark) which houses the study’s data collection forms is password-protected. The project principal investigators only have direct access to their own site’s data sets.

Records of each participant's identity and personal information will not be made public. Employees from Good Clinical Practice (GCP), Danish Health and Medicines Authority, and the corresponding foreign authority will have access to participants’ medical records and information collected in connection with the study for quality control (monitoring, audit, and inspection) of the project. GCP is independent from the sponsor and competing interests and will serve as a liaison between all three hospitals and the data manager, ensuring continuity. GCP has direct access to all three sites’ data sets and as such, will work with the data manager to oversee the intra-study data sharing process. A Data Monitoring Committee (DMC) with [name] [name] as chair (ICU), [name] [name] (centre for thrombosis), [name] MD, EDIC (ICU), and [name] [name] (statistician) has been established. The DMC is independent of those conducting, sponsoring, or funding the FBI trial. The DMC members are required to indicate their assent, as well as to declare any competing interests in the FBI charter. This charter which details the DMC’s roles and responsibilities, and planned method of functioning is available on request from the FBI study office.

